# **Supplementary Appendix Study Protocol: Safety and efficacy of aspirin-clopidogrel in acute non-cardiogenic minor ischemic stroke: a prospective and multicenter study based on real-world (SEACOAST)**

## **Introduction and rationale**

Although cerebrovascular disease is the second most common cause of death in the world, it is the leading cause of death in China. Stroke has become a major public health problem that seriously impacts the national economy and people's livelihood in China because of its high incidence and recurrence rate and high rate of disability, complications, and mortality. Presently, the diagnostic criteria of minor ischemic stroke (MIS) lacks consensus among researchers. A NIHSS score  $\leq 3$  or  $\leq 5$  is considered to indicate MIS. The results of the 2012 CHANCE study showed that early dual antiplatelet therapy with aspirin plus clopidogrel within 24 hours of onset could effectively reduce the relative risk of recurrent stroke by 32% without an increased risk of hemorrhage for patients with MIS (NIHSS  $\leq 3$ ) or high-risk transient ischemic attack (ABCD2  $> 4$ ). The findings of the CHANCE study were confirmed in the POINT trial, and both enrolled patients with NIHSS scores  $\leq 3$  within 24 or 12 hours after onset. At present, intravenous thrombolysis therapy or intravascular mechanical thrombus therapy can lead to neurological function improvement, which is defined by a NIHSS score  $\leq 5$ . A NIHSS score of 5 indicates the beginning of disability. However, whether thrombolysis is recommended for patients with a NIHSS score between 3 and 5 remains controversial, especially if deficits are not disabling. Early dual antiplatelet therapy may also be effective for secondary stroke prevention. However, if a stroke patient has a NIHSS score between 3 and 5 and an onset of 24 to 72 hours, the benefit of DAPT is unclear. This subgroup of stroke patients was not studied in the CHANCE or the POINT trial. Our questionnaire survey of neurologists showed that approximately 23% of patients with NIHSS scores  $\leq 5$  were treated with DAPT. Approximately 18% of neurologists would choose DAPT for patients with an onset within 24-72 hours. Approximately 52% of neurologists prescribed DAPT for patients with a NIHSS score between 3 to 5. Our single-center retrospective study of stroke patients with a NIHSS  $\leq 5$  and an onset time within 72 hours showed that 6.1% had recurrent strokes if treated with DAPT, compared to 10.8% in those who received aspirin only. Moreover, neurologists would

like to prescribe DAPT for stroke patients with a NIHSS score  $\leq 5$  and within 72 hours of onset. Therefore, there is a gap between the evidence found from two clinical trials and real-world clinical practice. The latest meta-analysis showed that stroke patients could benefit from receiving the benefits of DAPT could be used for stroke patients 3 days after onset, a time point at which deterioration of early neurological function would begin. A registry study in South Korea showed that more than 70% of patients (with  $4 \leq \text{NIHSS} \leq 7$ ) were treated with DAPT. Last, a subgroup analysis of the CHANCE trial showed that the proportion of ICAS in China was as high as 55.8%, indicating that large artery stenosis is a cause of ischemic stroke in Chinese patients. Research on the benefit of DAPT for stroke patients with higher NIHSS scores and the expanded time window to begin treatment is ongoing. However, the efficacy and safety of dual antiplatelet therapy for acute minor stroke (MIS patients with a NIHSS score  $\leq 5$  and onset within 72 hours) remain unclear. Our study on the safety and efficacy of dual antiplatelet therapy in patients with acute noncardiogenic minor ischemic stroke (NIHSS score  $\leq 5$ ) (SEACOAST) is a multicenter study of the application of DAPT in real-world practice.

## Methods

### Design

SEACOAST is a multicenter, nonrandomized, and prospective registry trial in China intended to demonstrate the efficacy and safety of dual antiplatelet therapy for acute minor stroke (with NIHSS score  $\leq 5$  and onset within 72 hours). The main aim of the present study is to test the hypothesis that dual antiplatelet therapy should reduce the incidence of 90-day stroke recurrence and improve the functional outcomes of patients with acute minor stroke (MIS patients with a NIHSS score  $\leq 5$  and onset within 72 hours) but should not increase the risk of symptomatic intracranial hemorrhage.

All patients who meet the enrollment criteria will be invited to participate. The study was approved by the Ethics Committee of the First Hospital of Shanxi Medical University. Written informed consent will be signed prior to enrollment. Participants will be divided into two groups: the dual antiplatelet therapy (DAPT) group and the single antiplatelet therapy (SAPT) group. Patients with acute minor stroke (NIHSS score  $\leq 5$ ) and onset within 72 hours, as judged by the investigators, who received

antiplatelet therapy at approximately 5-10 stroke centers in China between October 2019 and November 2021 were enrolled in the trial. The detailed inclusion/exclusion criteria as follow. Study recruitment started in September 2019, and the estimated primary completion date was November 2021.

### **Ethics and dissemination**

The patient or their guardian signed an informed consent form. The Ethics Committee of First Hospital of Shanxi Medical University approved the procedure, and approval was obtained from all other participating centers. The ethics approval number is 2019-SK004. The study protocol is registered at <https://www.chictr.org.cn>, Unique identifier: ChiCTR1900025214).

### **Study organization**

The initial protocol was designed by the SEACOAST group and discussed by the academic team. The Steering Committee was composed of the Shanxi Stroke Association. Neuroimaging associated with clinical events was performed centrally and interpreted by three independents blinded neuroradiologists. The trial is partially supported by the Shanxi Stroke Association.

### **Patient population (Inclusion/Exclusion Criteria)**

#### **Inclusion Criteria:**

- 1) acute minor ischemic stroke (NIHSS score  $\leq 5$  within 72 hours of symptom onset);
- 2) had been treated with antiplatelet drugs.
- 3) Informed consent signed.

(Symptom onset is defined by the “last seen normal” principle.)

#### **Exclusion Criteria**

- 1) Prestroke Modified Rankin Scale (mRs) Score  $> 2$  (premorbid historical assessment);
- 2) Diagnosis of hemorrhage or other pathology, such as vascular malformation, tumor, abscess or other major nonischemic brain disease (e.g., multiple sclerosis) on baseline head CT or MRI.
- 3) TIA;
- 4) Clear indication for anticoagulation (presumed cardiac source of embolus, e.g.,

- atrial fibrillation, prosthetic cardiac valves known or suspected endocarditis).
- 5) Patients who receive early intravenous thrombolysis or arterial thrombolysis;
  - 6) Currently or within 30 days before enrollment receiving an investigational drug or device.
  - 7) No use or use of other antiplatelet drugs (except aspirin, clopidogrel);
  - 8) Pregnant or lactating patients and patients planning to become pregnant within 90 days.
  - 9) Those with severe mental disorders, unable to provide informed consent or unable to cooperate with the follow-up due to dementia.
  - 10) Patients with complicated severe systemic disease with a life expectancy < 3 months.
  - 11) Planned or likely revascularization (any angioplasty or vascular surgery) within 3 months.

### **Sample size determination**

Our single-center study results indicated that the probability of stroke deterioration was approximately 10.8% in the aspirin group and 6.1% in the DAPT group. Considering the 10.8% recurrent stroke rate in the aspirin group and the 6.1% recurrent stroke rate in DAPT group, a p value < 0.05 indicating statistical significance at the 95% confidence interval, and a 10% drop out rate, the target number of participants will be at least 2500; PASS 22.0 will be used to perform sample size calculation.

### **Data collection**

Data were collected retrospectively using the Research Electronic Data Capture (REDCap), which is a secure web-based software platform that supports data capture for research studies by providing (1) an intuitive interface for validated data capture, (2) audit trails for tracking data manipulation and export procedures, (3) automated export procedures for seamless data downloads to common statistical packages, and (4) procedures for data integration and interoperability with external sources. All researchers are trained in a unified manner. Data are currently registered in the web-based registry available at <https://www.palacetrtrial.cn>.

The following data were directly obtained from the registry database: (1)

demographics, including age, sex, body mass index, smoking, admission systolic blood pressure (SBP), and diastolic blood pressure (DBP); (2) medical history, including previous TIA, previous stroke, previous coronary artery disease (CAD), previous peripheral artery disease (PAD), hypertension (HTN), diabetes mellitus (DM), dyslipidemia, smoking, and atrial fibrillation (AF); (3) previous medication, including previous antiplatelet, anticoagulated, antihypertensive and statins medication use; (4) stroke characteristics, including the time from onset to arrival (categorized as  $\leq 24$  hours and among 24 hours to 72 hours), initial NIHSS scores (categorized as  $\leq 3$  score and between 4 to 5 score), prestroke mRS score, and ischemic stroke subtype according to the TOAST criteria; (5) laboratory data, including white blood cell counts, creatinine serum levels, platelet counts, international normalized ratio (INR), urea, homocysteine (Hcy), and fasting low-density lipoprotein cholesterol (LDL-C); (6) in-hospital treatment, including antiplatelet, lipid lowering, antidiabetic and antihypertensive therapy, and (7) in-hospital imaging evaluation, including cranial MRI/CT examination and vascular examination (TCD/MRA/CTA/DSA) helped to determine the presence of intracranial cerebral atherosclerosis (ICAS), determined by 50%–99% stenosis of large intracranial arteries according to Warfarin-Aspirin Symptomatic Intracranial Disease (WASID) trial criteria; and (8) monitoring of some indicators, including daily blood pressure and blood glucose monitoring record results. For continuous variables, the missing value data were used by multiple imputation, and the optimal imputation data summarized after 5 interpolations were selected by the system for analysis.

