## **Statistical analysis**

Continuous variables that are normally distributed will be presented as the mean value and SD. When variables were not normally distributed, they were presented as medians and IQRs. Count data will be described with n (%). Student's t test was used for continuous variables, and the Pearson  $\chi^2$  test was used for categorical variables. To compare the survival curve and survival rate of stroke recurrence, survival analysis will be conducted. Cox proportional hazard models will be used to explore the risk

factors for recurrent ischemic stroke. Propensity score matching will be used to control for confounding factors. All analyses were performed in SPSS 26.0 and the statistical software package R (<http://www.R-project.org>, The R Foundation).

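### The plan analyses one imputed dataset that the software picks as optimal, instead of pooling all five, so standard errors are too small, mainly for the imputed covariates

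*Protocol*

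**What the plan says.** The missing-data rule stands at the end of the Data collection section of the protocol. It opens: "For continuous variables, the missing value data were used by multiple imputation". It continues that "the optimal imputation data summarized after 5 interpolations were selected by the system for analysis". The number of imputations is therefore five, and what reaches the analysis is a single set described as optimal and chosen by the software. The protocol does not say what makes a set optimal.

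The same section lists the continuous variables to which the rule can apply: body mass index, blood pressure and a laboratory panel (white cells, creatinine, platelets, INR, urea, homocysteine, LDL cholesterol).

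The Statistical analysis section gives two uses for such covariates. For adjustment, "Propensity score matching will be used to control for confounding factors". For prognosis, "Cox proportional hazard models will be used to explore the risk" factors for recurrent ischemic stroke. It does not mention combining estimates or variances over the five imputations.

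**The concern.** Multiple imputation gives valid standard errors because the analysis is run in every completed dataset and the spread of the results is added to the variance. That spread, the between-imputation variance, measures how uncertain the filled-in values are. If one completed dataset is analysed, the filled-in values are treated as observed and this part of the variance is lost. No imputed set is the best one, since each is a random draw from the same distribution. Averaging the five into one completed dataset does not help: it is still one dataset with no between-imputation component, and the averaged values vary less than real measurements would.

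At stake are the confidence intervals and p-values of the adjusted analyses. Those most exposed are hazard ratios for variables that were themselves imputed. The treatment contrast is exposed only indirectly, through adjustment, because treatment group and the primary composite event are not continuous variables. As optimal is undefined, a reader also cannot reproduce which set was used.

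**Working it through.** The protocol gives no figure to reproduce here except the number of imputations, m = 5. The consequence was checked by formula and by simulation.

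**Inputs from the protocol.** m = 5 and continuous variables only (Data collection). Size: "the target number of participants will be at least 2500" (Sample size determination). Planning rates: "the 10.8% recurrent stroke rate in the aspirin group" and "the 6.1% recurrent stroke rate in DAPT group" (same section).

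**Assumptions.** No missing-data rate is stated, so a range is used. The overall event rate is set at about 10%, near the upper planning rate.

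**By formula.** Let W be the within-imputation and B the between-imputation variance, scaled so that W + B = 1, and let the fraction of missing information be λ = B.
- Rubin's total variance with five imputations: T = W + (1 + 1/5)B.
- Standard error from one dataset: √W.
- True variance of an estimate from one dataset: about W + 2B.

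For λ = 0.20, T = 0.80 + 1.2 × 0.20 = 1.04. The ratio of one-dataset to pooled standard error is √(0.80/1.04) = 0.88. True coverage of the nominal 95% interval is 2Φ(1.96 × √(0.80/1.20)) − 1 = 2Φ(1.60) − 1 = 89.0%.

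| λ | SE ratio, one dataset / pooled | True coverage of 95% interval |
|---|---|---|
| 5% | 0.97 | 93.8% |
| 10% | 0.94 | 92.4% |
| 20% | 0.88 | 89.0% |
| 30% | 0.81 | 85.0% |

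λ applies to each parameter separately. It is close to the missing rate for the imputed covariate's own coefficient and much lower for the treatment effect.

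**By simulation.** Settings: 2500 patients, about 10% events, no treatment effect, one continuous confounder missing completely at random, proper normal imputation with m = 5, and 1500 replicates per setting. Logistic regression stands in for the Cox model. One dataset means an arbitrary one of the five.

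| Missing | Covariate: SE ratio | Covariate: miscoverage, one / pooled | Treatment: SE ratio | Treatment: type I error, one / pooled |
|---|---|---|---|---|
| 5% | 0.970 | 5.9% / 4.8% | 0.998 | 4.4% / 4.3% |
| 10% | 0.940 | 6.4% / 4.8% | 0.995 | 5.3% / 5.1% |
| 20% | 0.879 | 10.0% / 4.9% | 0.989 | 5.3% / 4.9% |
| 40% | 0.754 | 21.6% / 6.1% | 0.971 | 6.8% / 5.4% |

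The Monte Carlo standard error near 5% is √(0.05 × 0.95/1500) = 0.56 percentage points, so the treatment differences up to 20% missing cannot be told from zero. The treatment standard error is understated by 0.2% (1 − 0.998) to 2.9% (1 − 0.971).

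**Worst case.** If the dataset with the most extreme of the five results were the one analysed, type I error for treatment would be 5.2, 6.7, 8.0 and 11.1% at 5, 10, 20 and 40% missing.

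**Limit.** The simulation adjusts by regression, whereas the protocol names matching. A rougher check with 1:1 caliper matching (2500 patients, five of seven confounders incomplete, about 400 replicates per setting) gave one-dataset standard errors of 0.95, 0.94 and 0.93 of the pooled ones at 5, 10 and 20% missing per covariate. Type I error from an arbitrary dataset was not inflated (3 to 5%).

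**The case against.** The strongest objection is that the effect on the main question is small. Only continuous covariates are imputed, and at the trial's own size an arbitrary single dataset leaves the type I error for treatment close to 5% unless missingness is heavy. The large effects fall on covariate coefficients, in Cox models that the protocol describes as exploring risk factors. This stands, and it limits the severity.

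A second objection is linguistic: the clause is loosely worded, and its reference to summarizing could be a poor rendering of pooled output. That is possible, but a set that is optimal and is selected by the system does not describe Rubin's rules, and averaging would not cure the fault.

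A third is that a statistical analysis plan may give the details. It may, but the protocol does not leave this open. It fixes a rule, and a plan that pooled correctly would contradict it.

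Two stronger readings are tempting and are not supported. A reader might infer that the set most favourable to dual therapy would be chosen. The protocol attributes the choice to the software and says nothing of a choice made in view of the results, so the worst-case figures are an upper bound, not an expectation. A reader might also infer that patients with missing categorical confounders, such as stroke subtype or intracranial stenosis, drop out of the models. The protocol is silent on missing categorical data and does not list the propensity score covariates, so that would be a conclusion from silence.

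**Conclusion.** The rule is wrong as written and should be fixed. Analysing one completed dataset out of five, or an average of five, is single imputation and understates standard errors. The clear damage is to the effects of imputed covariates. There, miscoverage of a nominal 95% interval rises from about 6% at 5 to 10% missing to 10.0% at 20% and 21.6% at 40%, while pooling keeps it between 4.8 and 6.1%.

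For dual versus single antiplatelet therapy the effect is small. The documents do not support saying that the choice of dataset will drive the trial's result; that remains a possibility if much is missing or the choice is made with knowledge of the results.

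These sizes rest on an assumed missing rate, a single incomplete confounder missing completely at random, an event rate of about 10%, and logistic regression in place of the Cox model. The direction of the error does not depend on them.

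**What to change.** Delete the clause about the optimal set selected by the system. State instead that the propensity score, the matching and the outcome and Cox models are fitted in every imputed dataset, that estimates and variances are combined by Rubin's rules, and that no dataset is selected. The planned five imputations are enough to repair the fault: pooling them brought the error rates close to nominal in the simulation. A larger number is optional.

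The rule is written in the past tense. If a single set has already been analysed, the adjusted analyses should be rerun with pooling.

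The cost is modest. No new data or patients are needed, and R is already named in the Statistical analysis section. Intervals become slightly wider. Because the matched sample differs between imputations, balance tables and survival curves need some extra work and a stated convention for presenting them.

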### **Pharmaceutical regimen**

The study subjects were divided into two groups for comparison according to the initial antiplatelet regimen: single antiplatelet therapy (SAPT) with monotherapy of aspirin (dose of 81mg/100mg/200mg/300mg) or clopidogrel (dose of 75mg/150mg/300mg) and dual antiplatelet therapy (DAPT) with aspirin (dose of 81mg/100mg/200mg/300mg) plus clopidogrel (load dose of 75mg/150mg/300mg).

### **Data management**

Data quality control was divided into three parts: first, the patients' hospital information was retrieved from the electronic medical records system of each

subcenter; second, the trained researchers randomly performed cross data quality control every month; and third, three senior neurologists performed data quality control every month. We will use the data management system to manage the data. All data will be downloaded and analyzed at the First Affiliated Hospital of Shanxi Medical University.

### **Follow-up time**

The follow-up time for the two groups will be 90 days and 1 year. Vascular events were prospectively observed during hospitalization and during a 3-month follow-up period after the qualifying event via routine clinic visits or telephone interviews performed by experienced physicians with a predefined protocol. To ensure the accuracy of the outcome captured and to minimize inter-interviewer discrepancy, a set of uniform structured questionnaires was used by trained personnel. Enrollment will stop on November 31, 2021.

### **Outcomes**

We set a composite vascular event (ischemic stroke, TIA, symptomatic intracerebral hemorrhage, myocardial infarction or angina attacks, and vascular death) as the primary outcome at 90 days. Recurrent ischemic stroke: (1) sudden onset of a new focal neurologic deficit, with clinical or imaging evidence of infarction lasting  $\geq 24$  hours and not attributable to a nonischemic cause (i.e., not associated with brain infection, trauma, tumor, seizure, severe metabolic disease, or degenerative neurologic disease), and (2) a new focal neurologic deficit lasting  $< 24$  hours and not attributable to a nonischemic cause but accompanied by neuroimaging evidence of new brain infarction. Imaging indicated that the new infarct should be geographically distinct from the original infarct. Progressive ischemic stroke: rapid worsening of an existing focal neurologic deficit (NIHSS increasing  $\geq 4$ , excluding hemorrhagic transformation after infarction or symptomatic intracranial hemorrhage) lasting  $> 24$  hours and not attributable to a nonischemic cause, accompanied by new ischemic changes from the initial infarct on baseline magnetic resonance imaging or computed

tomography of the brain. Symptomatic intracerebral hemorrhage was defined as acute infiltration of blood into the brain parenchyma or subarachnoid space with associated neurological symptoms and imaging findings with an increase in the NIHSS score of four or more points. Any subject who had rapid resolution of symptoms and no brain imaging suggesting tissue infarction was considered to have had a TIA. Any patient initially diagnosed with stroke who did not have further brain imaging with evidence of infarction but had complete resolution of symptoms within 24 hours were considered to have had a TIA. Myocardial infarction was confirmed if one had more than two from below: typical chest pain, Troponin elevation, ECG changes (new ST segment changes, new Q wave, or new left bundle branch block). vascular death if definition as death due to vascular events. Further efficacy exploratory analysis of mRS score changes (continuous) was performed and dichotomized at percentages of 0 to 2 versus 3 to 6 at the 3-month and one-year follow-ups.

Safety endpoints included severe bleeding incidence (Global Use of Strategies to Open Occluded Coronary Arteries definition), including severe bleeding and symptomatic intracranial hemorrhage; moderate bleeding (Global Use of Strategies to Open Occluded Coronary Arteries definition). Moderate hemorrhage was defined as bleeding that required transfusion of blood but did not lead to hemodynamic compromise requiring intervention. Severe hemorrhage was defined as fatal or intracranial hemorrhage or other hemorrhage causing hemodynamic compromise that required blood or fluid replacement, inotropic support, or surgical intervention, and all bleeding events (intracerebral hemorrhage, skin bleeding, mucous membrane bleeding, gastrointestinal bleeding, and another visceral organ bleeding) during follow-up. All adverse events will be recorded.

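### The declared primary outcome is a 90-day vascular composite, but the hypothesis, the sample size and both named event analyses concern stroke recurrence

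*Protocol*

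**What the plan says.** Four sections of the protocol bear on the main endpoint.

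- **Outcomes.** The declaration reads: "We set a composite vascular event (ischemic stroke, TIA, symptomatic intracerebral hemorrhage, myocardial infarction or angina attacks, and vascular death) as the primary outcome". The time point is 90 days. The section then defines recurrent and progressive ischemic stroke as two separate events. The composite lists ischemic stroke without saying whether progressive stroke is included.
- **Design.** The main aim is to test that "dual antiplatelet therapy should reduce the incidence of 90-day stroke recurrence and improve the functional outcomes of patients with acute minor stroke". On safety, the same sentence adds that the treatment is expected to help "but should not increase the risk of symptomatic intracranial hemorrhage". The composite is not mentioned.
- **Sample size determination.** "Considering the 10.8% recurrent stroke rate in the aspirin group and the 6.1% recurrent stroke rate in DAPT group", with p < 0.05 and 10% dropout, the target is at least 2,500. The sentence before gives the same two rates under the name stroke deterioration.
- **Statistical analysis.** "To compare the survival curve and survival rate of stroke recurrence, survival analysis will be conducted". The next sentence begins "Cox proportional hazard models will be used to explore the risk", and the event whose risk factors it seeks is recurrent ischemic stroke. Chi-square and t tests are listed for categorical and continuous variables in general. Propensity score matching is listed without an endpoint.

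**The concern.** A primary outcome should be the quantity that the hypothesis names, the sample size supports and the main analysis estimates. Here these come apart. The composite has no hypothesis, no planning rate and no event analysis of its own. Stroke recurrence has all three and is not called primary. The one regression model named is described as a search for risk factors, not as the estimate of the DAPT effect.

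Two things are at stake. First, an analyst could report the composite, recurrent stroke or recurrent ischemic stroke as the main result and cite the protocol for each. Second, the power for the declared primary outcome cannot be read from the plan. The composite adds TIA, symptomatic hemorrhage, myocardial infarction or angina, and vascular death. These components need not respond to DAPT as ischemic stroke does, and symptomatic hemorrhage may move the other way.

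**Working it through.** **1. Endpoint by section**

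| Section | Endpoint |
|---|---|
| Design (hypothesis) | 90-day stroke recurrence; functional outcome; no increase in symptomatic intracranial hemorrhage |
| Sample size determination | 10.8% vs 6.1%, called both stroke deterioration and recurrent stroke |
| Outcomes (primary) | Five-part vascular composite at 90 days |
| Statistical analysis (event analyses) | Survival analysis of stroke recurrence; Cox model for recurrent ischemic stroke |

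Three sections broadly agree on stroke recurrence, and Outcomes differs from them.

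**2. The plan's own figure**

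Inputs from Sample size determination: p1 = 0.108, p2 = 0.061, alpha 0.05, 10% dropout. Power, sidedness and allocation are not stated, so I assume a two-sided test and a 1:1 split. With p̄ = (p1 + p2)/2 = 0.0845:

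n per arm = [1.96·√(2p̄(1−p̄)) + z_power·√(p1(1−p1) + p2(1−p2))]² / (p1 − p2)²

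- 80% power: 549 per arm; 1,098 in total; 1,098/0.9 = 1,220.
- 90% power: 734 per arm; 1,468 in total; 1,468/0.9 ≈ 1,632.
- 95% power: 2,018 after dropout. 99% power: 2,849.

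The figure of 2,500 matches none of these. It can be approached under unstated choices: for example, a 23% DAPT share, 90% power and a continuity correction give 2,487. It can be neither reproduced nor refuted. Whatever settings were used, the stated rates make it a calculation for recurrent stroke.

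**3. Power for the composite**

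The documents give no composite rates, so every case below is an assumption. All use 2,500 × 0.9 = 2,250 evaluable patients, 1,125 per arm, two-sided 0.05. The reference is recurrent stroke: RR = 6.1/10.8 = 0.565, power 98.0%.

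| Assumed effect of the added components | Rates, SAPT vs DAPT | Power |
|---|---|---|
| +2 points, same RR of 0.565 | 12.8% vs 7.2% | 99.3% |
| +4 points, same RR of 0.565 | 14.8% vs 8.4% | 99.8% |
| +2 points in both groups | 12.8% vs 8.1% (RR 0.63) | 95.4% |
| +4 points in both groups | 14.8% vs 10.1% (RR 0.68) | 92.2% |
| +1 point in both, DAPT excess of 1 point | 11.8% vs 8.1% | 83.5% |
| +1 point in both, DAPT excess of 2 points | 11.8% vs 9.1% | 55.3% |

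The direction of the change depends on how the added components respond to treatment.

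**4. False-positive risk from a free choice of endpoint**

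Recurrent stroke is treated here as nested in the composite. With p = 0.0845 (the mean planning rate) and composite rate q = p + 0.02 or p + 0.04 (assumed), the correlation is √[p(1−q)/(q(1−p))] = 0.89 or 0.81. The chance that at least one of two tests at 0.05 is significant under no effect, from the bivariate normal distribution, is then about 7% to 8%.

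**The case against.** The strongest reply is that the protocol does provide a test. Its chi-square test for categorical variables and its propensity matching are not limited to any endpoint, and a yes/no composite at 90 days is categorical. The details of the primary model may also sit in an analysis plan that is not shown. Part of this stands. A reader might infer that the primary outcome has no test at all, and the text does not support that. What remains is that the composite is assigned no event analysis. The generic chi-square is unadjusted in a nonrandomized comparison, and the event analyses that are named go elsewhere. An unseen plan could add detail, but it could not make the protocol's conflicting statements agree.

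Other stronger readings also fail:

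- **The study is underpowered for its primary outcome.** Not shown. Power could be higher or lower than for recurrent stroke, and equal additions of 2 to 4 points leave it at 92% to 95% under a 1:1 split.
- **The error rate reaches 14%.** That is 1 − 0.95³ = 0.143, which needs three independent endpoints. These are nested or overlap heavily.
- **Hemorrhage drops out of view.** It does not. Symptomatic intracranial hemorrhage is in the hypothesis and among the safety endpoints.
- **Functional outcome is left with only a t test.** The protocol also plans a dichotomized mRS (0–2 vs 3–6), which the chi-square test can serve. An ordinal model would be a preference.
- **The composite should give way to recurrent stroke.** Follow-up time ends enrollment in November 2021, and one reference carries a 2023 access date, so this text postdates enrollment. Demoting the declared primary outcome now could itself be a late endpoint switch.

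**Conclusion.** The contradiction is real and rests on the protocol's own wording. The endpoint declared primary is not the one that leads the hypothesis, sets the sample size or is the subject of the named event analyses, and the Cox model is not framed as the treatment comparison. The sample size statement does not support the declared primary outcome. Its power is unknown: 55% to 99.8% across the cases shown, against 98.0% for recurrent stroke, all under an assumed 1:1 split and assumed composite rates. If the headline may be either of the two nested endpoints, the false-positive risk is about 7% to 8%, not 5%.

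This does not show that 2,500 is wrong or too small, nor that any endpoint was chosen after results were seen. The point matters because it decides which result counts as confirmatory.

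**What to change.** Use one primary outcome in Design, Sample size determination, Outcomes and Statistical analysis. By default, keep the declared composite and then:

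1. State whether progressive ischemic stroke counts as an ischemic stroke event in the composite, and use one term for the events behind the 10.8% and 6.1% rates.
2. Make the primary analysis the comparison of DAPT with SAPT on time to the 90-day composite in the propensity-matched set.
3. Label recurrent stroke as secondary and the risk-factor Cox model as exploratory.
4. State that 2,500 was derived for recurrent stroke and not for the composite.

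If recurrent stroke was in fact the prespecified primary outcome before any data were seen, say so with the supporting record and make the composite secondary.

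The cost is wording only, with no new data. The team gives up the freedom to headline another endpoint and, if the composite stays, accepts that the stated sample size basis does not cover the primary outcome.
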